## Results

In the current study, 127 researchers across study sites received consistent training in clinical interviews, the use of wearable devices, and other psychological assessments. We randomly selected 46 researchers to complete a reliability assessment for 8 clinical structural interviews. The Cochran’s Q values ranged from 29.2 to 43.0, with all p-values > 0.05, indicating a high consistency among interviewers.

From November 28, 2022, to June 30, 2025, approximately 5000 individuals with suspected insomnia disorder were screened. A total of 3134 participants were interviewed, of whom 2937 (93.7%) were recruited and 197 (6.3%) were excluded. Among those recruited, there are 1743 (59.3%) from outpatient clinics and 1194 (40.7%) from community settings. The most common reason for exclusion was psychotic symptoms resulting from other mental disorders, which led to the inability to complete the clinical interview. The recruitment procedure is shown in Fig. 3.

All participants met the ICSD-3 criteria for insomnia disorder, with a mean age of 37.3 ± 12.6 years and 1952 (66.5%) were females. At baseline, 2850 participants (97.1%) were suffering from current insomnia disorder as defined by the clinical interview based on ICSD-3. In terms of comorbidities, assessed by the structured clinical interviews administered via the Zhiyoumian-Researcher app, 505 participants (17.2%) had current depressive disorders, and 613 participants (20.9%) had current anxiety disorders. The mean score of the ISI was 15.5 ± 5.8, with a median (interquartile range) score of 16.0 (7.0). When comparing those from the community setting and clinic, we found that the participants from the clinic are significantly older than their counterparts. But there is no statistical difference in sex, comorbidities, and insomnia severity (Table 2).

**Table 2 Tab2:** Demographics, comorbidities, and insomnia severity in participants from community and clinic settings（*N* = 2937）

	Community(*n* = 1194)	Clinic（*n* = 1743）	*p*
Age, mean±SD	35.9±12.3	38.2±12.3	＜0.001
Gender Female, n(%)	780 (65.3%)	1172 (67.2%)	0.283
Comorbidities, n(%)	364 (30.5%)	484 (27.8%)	0.115
Depressive Disorder	212(17.8%)	293(16.8%)	0.518
Generalized Anxiety Disorder	270(22.6%)	343(19.7%)	0.058
Bipolar Disorder	39(3.3%)	48(2.8%)	0.439
Panic Disorder	15(1.3%)	25(1.4%)	0.748
Post-Traumatic Stress Disorder	25(2.1%)	45(2.6%)	0.460
ISI, mean±SD	15.7±5.84	15.3±5.79	0.101
ISI ≥ 8, n(%)	1104(92.5%)	1602(92.9%)	0.625

Note: ISI, Insomnia Severity Index

In this EMA study, a total of 1231 participants (76.6%) provided eligible data for at least 50% of the time points, 1015 participants (63.2%) for at least 75%, and 746 participants (46.4%) for at least 90%. Furthermore, 2134 participants (72.7%) utilized accelerometers, while 2429 (82.7%) wore wearable EEG monitors for continuous assessments of their physical activity and sleep patterns. Of the 2850 participants with current insomnia, 2455 received e-CBTI treatment. Detailed data cleansing and analysis of the objective data will be reported elsewhere.

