### Interviewer training and the management system

The DIMOSI fieldwork was conducted by a team consisting of sleep researchers, psychiatrists, research assistants, and nurses. A study manager based at Guangdong Mental Health Centre, Guangdong Provincial People’s Hospital (Guangdong Academy of Medical Sciences) oversaw the supervisors and their teams. Among the four experienced supervisors, two were PhD-level psychiatrists (with 17 and 13 years of clinical experience, respectively), one was a postdoctoral sleep researcher (with 5 years of clinical research experience), and one was an MA-level clinical mental health researcher (with 2 years of clinical research experience).

Each interviewer conducting clinical assessment for participants was required to hold at least a bachelor’s degree and 2 years of experiences in clinical research. Interviewers were also required to complete a 20-hour General Interviewer Training (GIT) course before working on any DIMOSI survey, which included text, video, and on-site observational learning. Potential interviewers were required to pass an interview test before being allowed to contact participants. They needed to successfully complete three independent interviews under the supervision of two professional DIMOSI interviewers and had to pass a stringent examination. Failure was defined as making 3 or more errors out of the 393 test items.

In the pilot phase, we invited two centres to participate in the platform testing, involving a total of 98 subjects throughout the research process. Based on the issues encountered during testing, we refined quality control details and optimized software functionality. To ensure the system meets the needs of both participants and researchers, ongoing monitoring of the platform’s acceptability and usability will be conducted, including monitoring the apps, assessment scheme, hardware measurement devices, e-CBTI platform, and web management platform. After the official start of the study, real-time monitoring of backend data was implemented and participants were contacted if data stream disruptions occurred from any device to determine whether issues were related to functionality or user experience. Researchers conduct weekly quality control assessments, and provide feedback to each centre.

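### The stated high interviewer consistency rests on a non-significant Cochran's Q, which compares raters' positive-rating rates and does not measure agreement

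*Protocol article*

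**What the plan says.** The Results section of the protocol article describes the exercise: "We randomly selected 46 researchers to complete a reliability assessment for 8 clinical structural interviews". It then gives the result and its reading in one sentence, that the Cochran's Q "values ranged from 29.2 to 43.0, with all p-values > 0.05, indicating a high consistency among interviewers". The article does not state the degrees of freedom, the number of items behind each Q or the number of Q tests. It reports no kappa, intraclass correlation, percent agreement or confidence interval for the interviews.

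The section on interviewer training and the management system describes a separate check, a certification examination: "Failure was defined as making 3 or more errors out of the 393 test items". The Results section does not cite that examination as its evidence for consistency.

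**The concern.** The objection is to an inference printed in the article, not to a detail left for a fuller document. Two steps in it fail. A test of equal positive rates is used as a measure of agreement, and failure to reject is used as proof of sameness.

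The interviews carry weight in this study. According to the Digital platform section, they determine the insomnia diagnosis and comorbidity. The diagnosis is an inclusion criterion (Study population), and mental disorders and symptoms are among the features for clustering (Multimodal data integration). The Strengths and limitations section lists diagnosis by face-to-face interview as a strength. If interviewers at 33 sites differed in how they rate the same case, this could blur subtypes or appear as change at follow-up. The reader is told that this risk has been examined and is small, but the statistic shown cannot establish that.

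**Working it through.** **Inputs.** From Results: k = 46 raters, 8 interviews, Q from 29.2 to 43.0, all p > 0.05. Assumed, because not stated: the raters are the compared conditions, so df = k - 1 = 45, and each Q is based on 8, 20, 50 or 393 binary items (393 is the size of the certification test).

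**Step 1: reproduce the article's p-values.** Upper tail of the chi-square distribution:

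| df | p at Q = 29.2 | p at Q = 43.0 | 5% critical value |
|---|---|---|---|
| 45 (raters compared) | 0.967 | 0.557 | 61.66 |
| 7 (interviews compared) | 0.00013 | below 0.00013 | 14.07 |

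Only the first row fits the reported p-values; Q = 43.0 needs at least 30 degrees of freedom for p > 0.05. The figure reproduces with df = 45.

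**Step 2: what Q responds to.** Let G_j be rater j's number of positive ratings and L_i the number of raters positive on item i. Then

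Q = k(k - 1) Σ(G_j - mean G)² / Σ L_i(k - L_i).

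An item on which all 46 raters agree (L_i = 0 or 46) adds nothing to numerator or denominator, so Q ignores unanimous agreement. If raters are interchangeable, then given the item totals the expected value of Σ(G_j - mean G)² is Σ L_i(k - L_i)/k. Hence

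E(Q) = k(k - 1)/k = k - 1 = 45,

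whatever the level of agreement. The 95% range of chi-square with 45 df is 28.4 to 65.4, and both reported ends lie inside it.

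**Step 3: simulation.** 46 raters; 8, 20, 50 and 393 items; 1,500 to 3,000 runs per setting. In the rows with errors, half of the items are truly positive. Ranges are across item counts.

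| Raters | Mean Q | Share of runs with p > 0.05 | Fleiss' kappa |
|---|---|---|---|
| Random, 50% yes | 44.9-45.2 | 0.945-0.958 | about 0 |
| Random, 20% yes | 44.9-45.3 | 0.940-0.960 | about 0 |
| 20% errors | 44.5-45.3 | 0.950-0.963 | 0.33-0.36 |
| 10% errors | 44.8-45.0 | 0.955-0.961 | 0.60-0.64 |
| 5% errors | 44.9-45.1 | 0.953-0.968 | 0.78-0.81 |
| 2% errors | 45.0-45.4 | 0.945-0.970 | 0.90-0.92 |

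A single Q falls between 29.2 and 43.0 with probability 0.41 under chi-square with 45 df. The simulated probability is 0.39-0.42 for random raters. For 2% errors it is 0.40-0.41, except 0.24 with only 8 items, where Q is coarse.

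**Step 4: what Q can detect.** If 4 of the 46 raters say yes too often, p > 0.05 occurs in 60% of runs with 8 items, 14% with 20 and about 0% with 50 or more. If random raters' yes-rates vary around 0.5 with SD 0.10, the average of p(1 - p) is 0.25 - 0.01 = 0.24. With b items, mean Q is then approximately 45 × (0.24b + 0.01b²)/(0.25b) = 45 × (0.96 + 0.04b), which is 58 for b = 8, 79 for b = 20 and 133 for b = 50. Q therefore carries information about differing thresholds, increasingly so with more items, but not about agreement on individual cases.

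**The case against.** A reader might infer that interviewers answering at random would have produced these same values. That is too strong. It holds only if all raters share one positive rate, and then only as a statement about the distribution of Q. Random raters with differing rates would push Q up, as Step 4 shows. If there were eight independent Qs, the chance of all falling in 29.2-43.0 would be about 0.0008 (0.41 to the eighth power) under common-rate random rating. It would be similarly small under good agreement with independent errors, so this limits the wording without rescuing the article's inference.

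A reader might also infer that poor agreement would go unnoticed. The section on interviewer training describes a 20-hour course, supervised interviews, an examination that tolerates at most 2 errors in 393 items (2/393 = 0.51%), and weekly quality control with a checklist and feedback to centres. These are real safeguards against near-random interviewing. They do not measure inter-rater agreement, however, and are not what the Results section relies on.

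The reach should also be kept in proportion. The article does not say that all 127 trained researchers conduct diagnostic interviews. Nor does it say that the anxiety and depression outcomes in Longitudinal modeling are interview-defined; PHQ-9 and GAD-7 are collected at every visit. Interview data are one input among several, and no effect on the subtypes has been shown. Fuller agreement statistics may exist in material not shown, but that would not make the printed inference valid.

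**Conclusion.** The point holds in a limited form. The conclusion of high consistency does not follow from the statistic reported. Q between 29.2 and 43.0 on 45 df is ordinary for raters with a common positive rate, whether kappa is about 0 or about 0.9, and supports only that no difference in positive-rating rates was detected.

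Nothing here shows that agreement was poor, and the published figures do not allow kappa to be computed. The conclusion rests on df = 45, which is inferred but is the reading that fits the reported p-values. It does not depend on the number of items, although the simulated kappa values depend on the assumed prevalence. It is a wrong inference about a quality check; it does not alter the planned analysis or the sample size.

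**What to change.** Re-analyse the existing reliability ratings with a chance-corrected agreement coefficient (Fleiss' kappa, or Gwet's AC1 where a diagnosis is rare) together with percent agreement, each with a 95% confidence interval. With only 8 interviews, a per-diagnosis estimate may be very imprecise, or undefined where no case is positive; pool items there and say so. State the rated unit, the number of items and the degrees of freedom, and replace the sentence in Results.

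At minimum, restate the conclusion as no detected difference in positive-rating rates between interviewers. If agreement proves low, add a sensitivity clustering that leaves out the interview-based features.

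The cost is a re-analysis of data already collected. The reported reliability may turn out less favourable, and its interval may be wide.

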## Discussion

The DIMOSI study is a large-scale, national prospective cohort study on insomnia disorder in China. Several characteristics of the DIMOSI study, including its large sample size, prospective design, the integration of both subjective and objective assessments, and recruitment from both community and outpatient clinics across 33 centres in China, provide a unique opportunity to explore subtypes of insomnia disorder, as well as new prevention and intervention methods. All interviewers were well-trained and compliance with most assessments was satisfactory. Over 95% of participants had a current diagnosis of insomnia disorder, and nearly 20% had concurrent mood and/or anxiety disorders. The profile of the sample of the current study, for instance female dominance, is consistent with the previous epidemiological study [78, 79]. The majority of participants completed self-reported questionnaires, structured diagnostic interviews for mental and sleep disorders, cognitive function tasks, ecological momentary assessments, and continuous objective assessments of sleep and physical activity over a 7-day period.

This study is conducted on a digital multi-modal platform that integrates key research processes, including interviewer training and assessment, participant inclusion and exclusion criteria, ethical notifications, questionnaire assessments, cognitive task completion, and objective data collection. The platform is consistently used in both baseline and follow-up phases, ensuring a unified approach throughout the study. By utilizing this platform, the study maintains consistency in data collection across all stages, thereby enhancing both the quality and reliability of the research data. Additionally, all key aspects of data quality control are effectively managed within this digital platform. The application of the digital platform not only significantly improves research efficiency but also ensures consistency in operational processes at every stage, minimizing manual errors to the greatest extent possible. The use of the digital platform facilitates the accurate collection of multi-modal data from the real world and enables the integration and analysis of large datasets using advanced algorithms.

Research has found that insomnia disorder is a 24-hour condition [80], encompassing not only nighttime sleep disturbances but also daytime cognitive decline and alterations in circadian and activity patterns [81–83]. In our study, we used accelerometers and wearable EEG devices as objective assessment tools to measure sleep quality and rest-activity patterns. We did not use PSG because it is time-consuming and labor-intensive, and one single-night PSG assessment may not adequately capture the day-to-day variations in sleep conditions. We did not include biological sample (e.g., cortisol and melatonin) tests because of lacking reliable biological markers for insomnia disorders currently. Excluding biological samples does not affect our ability to test the research hypotheses.

This promising insomnia cohort, with a target sample size of 4,000, aims to provide sufficient statistical power for subtyping insomnia disorder. Additionally, we collect a series of objective multimodal data. Compared to previous studies using accelerometers to assess the sleep phenotype [84, 85], the current study offers insights into clinical and subthreshold symptoms, as well as cognitive functions [86, 87], which have potential clinical implications. In addition, the current cohort has the potential to clarify the associations of insomnia with other medical conditions and their underlying shared mechanism, enhancing the identification of at-risk individuals and prevention development. For example, given the established bidirectional relationship between insomnia and suicidality, the identification of distinct insomnia subtypes holds significant broader implications [88, 89]. Therefore, this study is likely to fill the knowledge gap in the understanding of insomnia disorder, particularly in the area of clinical subtyping.

## Strengths and limitations

The DIMOSI study has several notable strengths. First, the current study is a prospective cohort with a nationally representative large-scale sample recruited from both the community and clinical settings. All participants met diagnostic criteria through face-to-face clinical interviews based on ICSD-3 standards. This provides a sufficient number of representative participants, enabling the exploration of systematic subtypes and the assessment of their stability and predictive value. Second, the study employs comprehensive assessments, including traditional subjective measures, cognitive function evaluations, and objective measures of sleep and physical activity. Third, the integrated digital platform broadens the application scenarios in terms of time and location, making assessments of insomnia disorder more convenient and improving participant compliance.

However, several limitations of this study should be acknowledged. First, some participants were using sleep medications at baseline, which may have resulted in lower ISI scores at enrollment. We recorded these conditions and used statistical techniques to control for these factors. Second, considering that the main aim of this study is to analyze the subtype analysis of insomnia disorders rather than biological markers, biological sample testing was not included [90]. Third, while the comprehensive application of digital technology has conferred efficiency and high data quality, it may exclude some patients who are unable to use electronic devices. Finally, the current study uses convenience sampling, which may have introduced selection bias and limited generalizability, but we mitigated this via screening logs and community-clinic sensitivity analyses.

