## Methods

The Digital Multi-modal Approaches to Subtyping Insomnia Disorder (DIMOSI) study is a national prospective cohort study recruiting 4,000 individuals with a lifetime history of insomnia disorder from both clinical and community settings. Clinical setting includes outpatient clinics of psychiatry neurology, and sleep, while the individuals recruited from community health centers, promotional posters, and social media are recognized to be the participants from community setting. Participants will be invited to complete assessments via a digital platform, which includes data collection through smartphones, accelerometers, (Axivity AX3) and the wearable electroencephalogram (EEG) monitors for the comprehensive multi-modal evaluation of insomnia disorder and its related characteristics at baseline and follow-up points.

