### Study procedures

Each site adopted systematic convenience sampling, screening for all eligible participants from both community and clinical sources who are willing to join the study. Screening logs and reasons for exclusion are documented to evaluate potential selection bias. Standardized recruitment and assessment procedures are implemented uniformly across all participating sites. Figure 3 illustrates the recruitment process for the study. Potentially eligible individuals will be screened through either outpatient clinic or community settings. Research assistants will contact these individuals to provide a brief explanation of the study objectives and conduct a preliminary eligibility assessment. Those deemed potentially eligible will be invited to the nearest study site for confirmation of eligibility and a face-to-face baseline assessment.

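### The sample is described as nationally representative, but every site recruited by convenience sampling, so the design does not have that property

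*Protocol article*

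**What the plan says.** The Strengths and limitations section opens its strengths with a "nationally representative large-scale sample recruited from both the community and clinical settings". Two sentences later it adds: "This provides a sufficient number of representative participants, enabling the exploration of systematic subtypes", and goes on to the stability and predictive value of those subtypes.

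The Study procedures section states the sampling method: "Each site adopted systematic convenience sampling, screening for all eligible participants from both community and clinical sources who are willing to join the study". The opening paragraph of Methods says how the community arm was reached: "the individuals recruited from community health centers, promotional posters, and social media are recognized to be the participants from community setting". The Study population section describes 33 sites that specialise in psychiatry, neurology or sleep medicine.

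The limitations paragraph, directly after the strengths, concedes that "the current study uses convenience sampling, which may have introduced selection bias and limited generalizability", and adds that "we mitigated this via screening logs and community-clinic sensitivity analyses".

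**The concern.** National representativeness is a property of how people enter a sample. It needs either selection from a defined frame with known probabilities, or an adjustment that ties the sample to known population figures. The article states a method that provides neither, and then claims the property as its leading strength.

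What is at stake is how the results are read. Subtyping is the primary outcome, and the Subtyping procedures section describes a single feature matrix with no split by setting. A reader told that the sample represents the country could take the relative size of the subtypes, or their outcome rates at 6 and 12 months, as figures for people with insomnia disorder in China. The design does not support that reading.

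**Working it through.** This is mainly a comparison of statements, with a little arithmetic on the recruited mix.

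**1. The statements side by side.**

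| Place | What is stated or described |
|---|---|
| Strengths and limitations, first strength | The sample is nationally representative; participants are representative |
| Study procedures | Convenience sampling at each site, of eligible people willing to join |
| Methods, opening paragraph | Community arm reached through health centres, posters and social media |
| Study population | Specialist sites; participants must be able to use the study devices |
| Strengths and limitations, last limitation | Convenience sampling, with possible selection bias and limited generalizability |

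Rows two to five agree with each other. Row one conflicts with them. Because the sampling method is stated outright, this is a contradiction and not a detail left to a fuller document.

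**2. Does the stated mitigation restore the property?** Screening logs can describe who was not enrolled, but they do not change who was. The community-clinic comparison can show whether two volunteer groups resemble each other. It cannot show that either resembles the national population.

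**3. Does the sample size restore it?** The target of 4,000 comes from 50 events per variable × 80 variables = 4,000, which reproduces the stated figure. That rule concerns model fitting and has no bearing on how people were selected.

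**4. The recruited mix.** From Results: 1,743 / 2,937 = 59.3% from clinics and 1,194 / 2,937 = 40.7% from the community. Both reproduce. Recruitment set this mix, and it is an interim count against a target of 4,000.

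**5. How the mix enters a subtype share.** Let w be the clinic fraction, and p1 and p2 the shares of a subtype among clinic and community participants.

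- Pooled share = w × p1 + (1 − w) × p2.
- Gap between the recruited mix and a population with clinic fraction v = (0.593 − v) × (p1 − p2).

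The gap is zero if p1 = p2 and grows with the difference between settings. The number of participants does not appear in it, so a larger cohort does not shrink it. The article gives neither v nor the setting-specific shares, so no value can be put on the gap. It also covers only the mix of settings. Self-selection within each setting would come on top and is equally unknown.

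**The case against.** The strongest reply is that the article discloses the limitation. It names convenience sampling in the methods, keeps screening logs to examine selection, and concedes limited generalizability one paragraph after the claim. No section announces a national prevalence or a national subtype share: the aims are to identify subtypes, test their stability and predictive accuracy, and follow their course. On this view, what remains is one over-favourable phrase. Most of this stands, and it limits the point to a wrong label and its interpretation. It does not make the label true.

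The available data also show the settings to be similar. In Table 2, mean ISI is 15.7 in the community and 15.3 in the clinic, the female share 65.3% and 67.2%, and any comorbidity 30.5% and 27.8%. Only age differs significantly (35.9 and 38.2 years). This is a fair reason not to presume a large effect of the mix. It does not establish that subtype shares are equal, and it says nothing about either group against the population.

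The sentence about representative participants directly follows the one on face-to-face ICSD-3 diagnosis, so its opening word may refer to diagnostic confirmation and not to sampling. That is possible. The word representative is unsupported on either reading.

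A reader might also treat the 2,937 recruited out of about 5,000 screened as evidence of heavy self-selection. The article does not support that. Those screened had suspected insomnia and may include ineligible people, so the ratio is not a participation rate. Of the 3,134 interviewed, 93.7% were recruited.

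**Conclusion.** The point holds as a contradiction in the text. The article claims national representativeness, states a sampling method that cannot deliver it, and concedes the consequence in the next paragraph. Having 33 sites across China makes the study national in reach, which is a different property.

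Two stronger readings are tempting. The first is that the study plans to report wrong national figures or that its subtypes are invalid. The analysis plan contains no population estimate, and identifying subtypes and comparing participants within the cohort do not require a representative sample. The second is that subtype shares are wrong by a known amount. No population clinic share and no setting-specific subtype share is given, so the size of any bias cannot be computed.

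What remains is conditional: if subtype shares or outcome rates differ between settings, the pooled figures reflect the recruited 59.3:40.7 mix (interim) and should not be read as national. This rests on the article's own description of sampling and on its describing no weighting.

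**What to change.** Four changes, all in wording or in reporting already foreseen:

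1. In Strengths and limitations, describe the cohort as a large multicentre convenience sample from sites across China, in place of a nationally representative one.
2. In the sentence "This provides a sufficient number of representative participants", delete the word representative.
3. State that subtype proportions and outcome rates describe the recruited cohort and are not national estimates.
4. Within the community-clinic sensitivity analyses the article already mentions, show subtype proportions separately by setting, so that readers can see whether the mix matters.

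Setting is already recorded for every participant, so no new data are needed. The sampling design does not change. The one real cost is that the first stated strength becomes less favourable.
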